#### The implementation method

The researcher will implement the designed program after obtaining the necessary coordination with authorities of four gynecology training clinics covered by Shiraz University of Medical Sciences. This is done by referring to the gynecology training clinics and presenting a letter of introduction to the authorities of those centers regarding research objectives. After that, the researcher will be allowed to access to phone numbers of adolescent girls with PCOS and call her in order to explain research objectives and invite them to participate in the research. If they are willing to cooperate, and have all the inclusion criteria, they will be selected by convenience sampling method with their informed consent.

Adolescent girls^,^ knowledge, attitude, subjective norms, perceived behavioral control, behavioral intention and eating practice (behavior) will be considered as the suggested outcomes. Before intervention, the questionnaires will be filled by them in each of the two groups. Furthermore, the questionnaires will be refilled by adolescent girls with PCOS three months after the intervention.

#### Data analysis

The collected data will be analyzed by descriptive statistical methods (mean, standard deviation, minimum, and maximum), inferential statistics (paired t-test, t-test, Chi-squared test, Fishers exact test, Wilcoxon test, and Mann-Whitney test), and SPSS Version 20.0 software. ANCOVA will be used for adjusting intervening variables.

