#### Sample size

Sample size will be 36 participants in each group considering 95% confidence interval, 80% trial power, S = 0.1–0.25 and 10% loss.

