#### Sampling method

This clinical trial has one intervention group and one control group. After identifying the clinics covered by Shiraz University of Medical Sciences, four gynecology training clinics will be selected non-randomly. Afterwards, 18 adolescent girls with PCOS with inclusion criteria will be selected from each center via convenience sampling method.

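### The test list does not say which comparison carries the conclusion, and ANCOVA is tied to undefined covariates rather than to the baseline score already collected

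*Protocol article*

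**What the plan says.** All references are to the third (quantitative) phase of the protocol article.

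- **The implementation method:** six outcomes are named (knowledge, attitude, subjective norms, perceived behavioural control, behavioural intention and eating practice). "Before intervention, the questionnaires will be filled by them in each of the two groups". The same questionnaires are repeated three months after the intervention.
- **Data analysis:** the plan is descriptive statistics plus "inferential statistics (paired t-test, t-test, Chi-squared test, Fishers exact test, Wilcoxon test, and Mann-Whitney test". No test is attached to an outcome or to a comparison. The next sentence is "ANCOVA will be used for adjusting intervening variables". The variables are not listed.
- **Sample size:** "Sample size will be 36 participants in each group", with "S = 0.1–0.25 and 10% loss".
- **Sampling method:** "This clinical trial has one intervention group and one control group". Eighteen girls come from each of four clinics by convenience sampling. The text shown describes no random allocation.

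**The concern.** Each outcome has one baseline and one follow-up value, so the natural effect estimate is a between-group difference at three months, adjusted for that outcome's own baseline. The plan has the data and the method but does not join them. It leaves three things open.

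1. **Which test is the effect test.** Paired tests describe change within an arm and do not compare the arms. They stand beside two-sample tests with no rule on which decides.
2. **Whether the two-sample test uses baseline.** The t-test and Mann-Whitney test could be applied to three-month scores alone or to change scores. Used alone, three-month scores discard information in a trial of 72 girls and carry any baseline difference into the estimate.
3. **What ANCOVA adjusts for.** The baseline score is not identified as the covariate. The term used is loose enough to admit variables measured after the intervention.

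These choices can give different answers from the same data, and the current wording permits all of them.

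**Working it through.** **Inputs from the article.** 36 per group, 10% loss, 80% power and 95% confidence. I read the last as alpha 0.05; two-sided is my assumption.

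**Inputs assumed.** A true effect of 0.5 SD and r = 0.3 to 0.7. The article gives neither.

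**The plan's own figure.** 36 per group cannot be derived, because no target difference is stated. Only the loss step checks: 32 / 0.9 = 35.6, rounded up to 36. Working back, 32 evaluable per arm gives 80% power (normal approximation) for a standardised difference of √(2 × (1.960 + 0.842)² / 32) = 0.70. The point here does not depend on this.

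**Power at 0.5 SD.** Evaluable n per arm = 36 × 0.9 = 32.4. The residual SD factor f, relative to the outcome SD, is:

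- three-month score only: f = 1
- change score: f = √(2(1 − r))
- baseline ANCOVA: f = √(1 − r²)

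Non-centrality = (0.5 / f) × √(32.4 / 2) = 2.012 / f, with about 63 degrees of freedom. Losing one degree of freedom to the covariate changes power by less than 0.1 percentage point.

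| r | Three-month only | Change score | Baseline ANCOVA |
|---|---|---|---|
| 0.3 | 51% | 39% (f = 1.183) | 55% (f = 0.954) |
| 0.5 | 51% | 51% (f = 1.000) | 63% (f = 0.866) |
| 0.7 | 51% | 73% (f = 0.775) | 79% (f = 0.714) |

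ANCOVA is the most powerful of the three throughout this range. Its lead over the better alternative is 4, 12 and 6 percentage points.

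**Baseline imbalance** (simulation, 32 per arm, no programme effect). Two situations point in opposite directions.

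- *The three-month score depends on baseline alone.* With a systematic baseline gap of 0.25 or 0.5 SD, the three-month-only t-test is falsely significant in 8% or 16% of trials at r = 0.5, and in 11% or 27% at r = 0.7. ANCOVA stays near 5%.
- *A stable gap of 0.5 SD simply persists.* ANCOVA is falsely significant in about 18 to 19% of trials at r = 0.5 and 13% at r = 0.7. A change-score test stays near 5%.

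**If paired p-values were compared across arms.** Suppose both arms improve equally, with n = 32 per arm and r = 0.5. If q is the power of one paired test, the chance that only the intervention arm is significant is q(1 − q). For common changes of 0.1, 0.2, 0.3, 0.4, 0.5 and 0.6 SD this is 8%, 16%, 23%, 24%, 17% and 8%. It can never exceed 25%.

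**Adding clinic.** Four clinics × 18 = 72 = 2 × 36. A model with intercept, group, baseline score and three clinic indicators has six columns. If two whole clinics form each arm (2 × 18 = 36), its rank is 5 and the group effect cannot be estimated. If both arms occur within every clinic, its rank is 6.

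**The case against.** The strongest defence is that ANCOVA is already planned, that nothing excludes the baseline score from it, and that covariate lists are commonly left to a statistical analysis plan or full protocol. This partly stands: the authors may well mean baseline variables, and it would be wrong to say that the plan rules out baseline adjustment. But the article did choose its tests and did give ANCOVA a role, and what it wrote allows conflicting analyses. That is a point fixed badly, not just detail omitted for space.

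Two stronger readings are tempting, and the article supports neither.

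- A reader might infer that three-month knowledge, attitude, norms, control or intention will be covariates, which would remove part of the programme's effect on eating practice. The article lists all five as dependent variables and outcomes and nowhere says they will be adjusted for.
- A reader might infer that the effect will be judged from paired p-values. The list also contains between-group tests, and using paired tests descriptively fits the text.

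Both are risks of the wording, not stated intentions.

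Three further objections stand. Against a change-score t-test the gain at r = 0.7 is 6 points (73% to 79%), not 28. At r = 0.3 the gain over three-month scores alone is only about 4 points. And without described randomisation, ANCOVA is not guaranteed to be unbiased, as the persisting-gap simulation shows.

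**Conclusion.** The point holds as a defect of specification that should be corrected. The plan names no main between-group analysis and gives ANCOVA to undefined covariates, while the most useful covariate is collected for every outcome in both groups.

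At a true effect of 0.5 SD and about 32 evaluable per arm, naming baseline-adjusted ANCOVA raises power from 51% for three-month scores alone to about 55%, 63% or 79% at r = 0.3, 0.5 or 0.7. The correlation and the effect size are assumptions, so the size of the gain is uncertain. Its direction is not in doubt over this range.

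The conclusion does not extend to freedom from bias. With convenience sampling and no allocation method described, baseline adjustment deals with one measured source of imbalance and leaves unmeasured confounding in place.

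**What to change.** Rewrite the Data analysis section as follows.

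1. For each outcome, the main between-group analysis is an ANCOVA of the three-month score on group and the same outcome's baseline score, reported as the adjusted difference with 95% CI.
2. Replace the phrase about intervening variables with a list of covariates named in advance and measured before the intervention.
3. Add clinic only if both arms occur within each clinic; otherwise clinic is aliased with group.
4. Paired t-tests and Wilcoxon tests (if signed-rank is meant) are descriptive only.
5. Mann-Whitney is a sensitivity analysis. Because no random allocation is described, a between-group change-score analysis is reported as a second one.
6. Do not claim that ANCOVA removes all confounding.

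The cost is wording. The baseline and three-month scores are already collected and ANCOVA is already planned. The one fact to settle first is how girls are assigned to arms across the four clinics, because item 3 depends on it.

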#### Integration of the qualitative and quantitative data

The results of the qualitative and quantitative phases of the study will be integrated and finally, a program for promoting eating behaviors in adolescent girls with PCOS will be provided.

## Discussion

One of the useful strategies for preventing diet-related chronic diseases is to modify and change eating behaviors. PCOS is one of these diseases that obesity and overweight has an important role in its occurrence, advancement and complications. Also obesity could aggravate all of the problems caused by this syndrome including infertility and metabolic problems [6]. Most of the studies have suggested weight loss and lifestyle modification as the first line treatment for this syndrome [12]. Therefore, it seems necessary to perform fundamental culturally sensitive society-based interventions in this field. In the present study sequential exploratory design will be used for providing an appropriate interventional program. Exploratory mixed method is a known method for performing researches, especially when little information exists about the studied phenomenon; it is also an appropriate method for achieving the experiences of the participants. When one method is not sufficient for revealing the research subject, it is better to use a mixture of both methods. Using mixed method would help the researcher to gain a comprehensive understanding of a phenomenon and would relate different aspects of a phenomenon to each other [17]. Since the subject of the present study has a new multi-dimensional nature and the researcher is not able to predict the effective factors on this subject, therefore it seems that using mixed method study and applying both the methods of qualitative and quantitative studies would be an appropriate method for achieving the goals of the study.

According to the studies, having healthy eating behaviors and a proper weight could significantly decrease the complications of PCOS in adolescent girls [6]. It is believed that improving and enhancing the health condition of the adolescents is much more difficult and complicated that other age groups. Although the mortality rate of the youth and adolescents is relatively low, they are usually involved with behaviors that could affect the quality of their health. However, their behaviors are not rooted and permanent and the ability to accept changes is more among them than the adults. So, the efforts toward the health of the adolescents must mostly consider preventive measures. Furthermore, prevention is a cost-effective strategy for adolescents and its benefits are long-lasting [18]. Therefore, it seems that, using the results of the present study and applying its suggested interventional program by adolescent girls, policymakers, health managements and families might have positive effects on administering and promoting healthy eating behaviors by adolescent girls with PCOS. If this program works, it can become one of the leading education guidelines for eating behaviors in adolescent girls with PCOS.

## Abbreviations

FFQ: Food frequency questionnaire
PCOS: Polycystic ovarian syndrome
